### Statistical methods

#### Sample size

Based on results of a previous study, a sample size of 47 participants per group was estimated to provide 80% power to detect a between-group difference of 2.4 m/s of conduction velocity improvement of common peroneal nerve, with a pooled standard deviation of 4.15 m/s and an alpha level of 0.05. The assumption of a conservative 20% drop-out rate in any group increases the sample size to 59 participants per group or 118 participants in total.

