#### Statistical analysis

Statistical analysis will be performed by an independent statistician who is not aware of group allocation. SPSS 21.0 (IBM SPSS Statistics, New York, USA) will be used for data analysis. Level of significance will be established at α < 0.05 with a two-sided test. Continuous data will be represented by mean ± standard deviation or median (range), and categorical data will be represented by percentage. All efficacy analyses will be performed using the intent-to-treat (ITT) approach. For the ITT analysis, population will consist of all patients who have been randomized. Missing data will be imputed using the last observation carried forward (LOCF) method. Continuous variables will be compared using Student’s *t* test or Wilcoxon rank-sum test as appropriate. Categorical variables will be compared using Fisher’s exact test or Wilcoxon rank-sum test as appropriate. Analysis of covariance (ANCOVA) or logistic regression will be used for analysis and adjustment of baseline characteristics that differ significantly between two groups.

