A suitable control group is critical for a well-designed clinical trial. On the basis of literature review, using a blunt-tipped needle that does not penetrate the patient’s skin is the most commonly used approach for administering sham treatments among acupuncture trials [16, 17]. Patients who have received acupuncture treatment in the last 3 months and can distinguish SA from MA will be excluded. The same control group design, no skin penetration at acupoints, was adopted and succeeded in masking patients with DPN [7, 14, 15, 18]. Furthermore, all patients will be asked to guess which treatment they have received to test patient-blinding effects at week 12.

The change of nerve conduction velocity is chosen as the primary outcome because it is the highest sensitive and objective method to detect neuropathy. Multiple systematic reviews [11] recommended nerve conduction velocity as a main outcome, and it had been widely used as an outcome measure in DPN studies [23]. At the same time, assessment of the severity of DPN mainly depends on patient-reported outcomes. The MNSI is the most DPN-specific patient-reported measure. In this trial, we use the DSQL to evaluate quality of life in patients with DPN before and after acupuncture treatment. The DSQL captures the impact of detailed aspects of modern diabetes management (e.g., carbohydrate counting and flexible insulin dose adjustment) that is extensively used in evaluating quality of life in DM. The DSQL offers a valuable tool for assessing the impact of treatment approaches on QoL in adults with DM [20].

The limitation of our trial is acupuncturists are not blinded for the nature of intervention. We hope results of this trial will provide more reliable evidence and clarify the value of acupuncture as a treatment for DPN.

To summarize, this trial meets the methodological demand of adequate randomization and allocation concealment, blinding of patients, outcome assessors, and statisticians. Findings of this study will provide high-quality evidences for evaluating the efficacy and safety of acupuncture treatment for DPN.

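### Covariate adjustment is triggered by a baseline significance test between randomised arms; adjusting for baseline peroneal MNCV in every case would add precision at no cost.

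*Protocol article*

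**What the plan says.** The Statistical analysis section of the Protocol article gives one rule for all continuous outcomes: "Continuous variables will be compared using" a t test or a Wilcoxon rank-sum test. Adjustment then follows only on a condition: "Analysis of covariance (ANCOVA) or logistic regression will be used for analysis and adjustment of baseline characteristics that differ significantly between two groups". No covariate is named in advance, and the primary outcome has no model of its own, so this general rule governs peroneal MNCV.

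The Primary outcome section has MNCV measured at baseline and at week 12. The Discussion describes the endpoint as a change: "The change of nerve conduction velocity is chosen as the primary outcome". The Sample size section powers the trial for a "between-group difference of 2.4 m/s of conduction velocity improvement of common peroneal nerve". The pooled SD assumed there is 4.15 m/s, at alpha 0.05. The test is two-sided: "Level of significance will be established at α < 0.05 with a two-sided test".

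**The concern.** Allocation is by concealed blocked randomisation, so any baseline difference between arms arises by chance. Its p-value says nothing about whether the variable predicts week-12 conduction velocity. A rule that adjusts only for what is significant has three consequences:

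- It leaves out baseline MNCV, the natural predictor of the outcome, unless that variable happens to cross the threshold.
- It can bring in irrelevant variables that do cross it.
- Nobody can write down the adjusted model until the baseline data have been seen.

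At stake are some precision in the primary comparison, the clarity of having one prespecified estimate, and protection against a chance baseline gap that falls just short of significance.

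**Working it through.** **Inputs.** From Sample size: difference 2.4 m/s in improvement, SD 4.15 m/s, alpha 0.05, 80% power, 20% dropout. From Statistical analysis: two-sided testing. Two readings are mine. First, 4.15 is taken as the SD of the change, which the text implies but does not state. Second, the baseline/week-12 correlation r is not given, so 0.5 to 0.9 is shown. Equal variance at the two visits is assumed.

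**The plan's own figure.** n = 2 × (1.960 + 0.842)² × (4.15/2.4)² ≈ 46.9, so 47 per arm. Then 47/0.80 = 58.75, so 59 per arm and 118 in total. Both stated figures reproduce, with no covariate in the calculation. By noncentral t, power at 47 per arm is 79.2%.

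**Always adjusting for baseline MNCV.** The ANCOVA residual SD is 4.15 × √((1 + r)/2). Noncentral-t power is for 47 per arm.

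| r | Residual SD (m/s) | ANCOVA power | Gain over change-score t test (79.2%) |
|---|---|---|---|
| 0.5 | 3.59 | 89.3% | 10 points |
| 0.7 | 3.83 | 85.3% | 6 points |
| 0.8 | 3.94 | 83.2% | 4 points |
| 0.9 | 4.04 | 81.2% | 2 points |

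**The plan's rule, simulated.** Each run tested baseline MNCV at 0.05, used ANCOVA if it was significant, and otherwise used a t test on change (40,000 runs per scenario, 47 per arm). The trigger fired in about 5% of trials. At r = 0.5, 0.7, 0.8 and 0.9:

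- Power under the rule was 80.4%, 80.3%, 79.5% and 79.3%.
- Power with ANCOVA in every trial was 89.0%, 85.3%, 82.8% and 80.9%.
- Overall type I error under the rule lay between about 0.043 and 0.049.

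**Chance selection of covariates.** If k independent baseline characteristics are each tested at 0.05, the probability that at least one triggers adjustment is 1 − 0.95^k. This is 23% for k = 5, 40% for k = 10 and 54% for k = 15. The values of k are illustrative.

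**A baseline gap just under significance.** At r = 0.7 the SD of a single MNCV measurement is 4.15/√(2 × 0.3) = 5.36 m/s. The two-sided threshold for the baseline difference is 1.986 × 5.36 × √(2/47) ≈ 2.2 m/s. A gap of 2.1 m/s would go unadjusted. It would shift the expected change-score difference by (1 − 0.7) × 2.1 ≈ 0.6 m/s, against the arm with the higher baseline. That is about a quarter of the 2.4 m/s target.

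**Under the planned analysis set.** All randomised patients are analysed with LOCF, and MNCV is measured only at baseline and week 12, so a missing week-12 value becomes the baseline value. I simulated 59 per arm with 20% carried forward at random (an assumption). The rule gives about 79% power at every r, and ANCOVA gives 86%, 83%, 81% and 80%. The gain shrinks to about 7, 4, 2 and 1 points.

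**The case against.** The strongest reply is that nothing the trial was designed to deliver is lost. The 80% power was computed for an unadjusted comparison of improvement, and the rule delivers it on that scale. A change score already subtracts baseline, so leaving baseline out as a covariate only fixes its coefficient at 1 instead of estimating it. That is why the gain fades as the correlation rises. The statistician is unaware of allocation, which limits steering. The ANCOVA sentence can also be read as describing a supplementary analysis. The 0.6 m/s shift is a near-worst case; averaged over randomisations the change-score estimate is unbiased. All of this stands, and it limits the size of the point.

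It does not rescue the trigger. Masking the statistician does not prespecify a model. Whether the adjusted analysis is primary or supplementary, its existence and content still depend on chance.

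Two stronger readings are tempting and not supported:

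- **Inflated false positives.** A reader might infer that a two-stage rule inflates type I error. In simulation it is slightly conservative.
- **Collapse of the planned power.** A t test on week-12 values alone would cut the rule's power to about 60% at r = 0.7 and 43% at r = 0.8. The Statistical analysis section does not name the analysed variable, but the Abstract, Sample size and Discussion all point to change from baseline. Those figures describe an analysis the document points away from.

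The choice between t test and Wilcoxon is detail that an article may leave to the full plan, and is not part of this point.

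**Conclusion.** The point holds as a modest one. The rule is stated in the article, so it is a rule fixed badly and not a missing detail. It selects covariates by chance and leaves the adjusted model undefined until baseline data are seen. It forgoes roughly 2 to 10 points of power at 47 per arm, or about 1 to 7 points with LOCF as simulated. A chance baseline gap just under significance can also stay in the estimate.

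Planned power on the change score and overall type I error are both intact, so a positive result under the stated rule would remain valid. The size of the gain rests on the assumed correlation, on reading 4.15 m/s as the SD of change, and on equal variances at the two visits. Its direction does not depend on the value of r, because under those last two assumptions the ANCOVA residual SD is below 4.15 for every r under 1.

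**What to change.** Replace the conditional adjustment sentence with wording such as: *The primary analysis is an ANCOVA of week-12 peroneal MNCV with treatment group and baseline peroneal MNCV as terms, fitted whatever the observed baseline balance, and reported as the adjusted mean difference with its 95% confidence interval. Each continuous secondary outcome that has a baseline measurement is adjusted for its own baseline in the same way.*

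Name any further covariates in advance, and delete significance testing of baseline differences as a trigger. The patients' global assessment is collected only at week 12 and has no baseline to adjust for.

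The cost is one or two sentences, to be settled before unblinding. The baseline values are already collected, and the sample size of 118 need not change.

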#### Ethics and dissemination

The study protocol which follows principles of the Declaration of Helsinki has been approved by the Medical Ethics Committee of Long-Hua Hospital affiliated to Shanghai University of Traditional Chinese Medicine since 7 July 2016 (Approval Number: 2016LCSY028) and registered on the Chinese Clinical Trial Registry, ChiCTR1800020444. Results will be disseminated through peer-reviewed publications, a master’s thesis, or conference presentations. Data will be anonymized prior to publication to prevent identification of individual participants.

## Discussion

Diabetes mellitus (DM) is a common disease which is accompanied by highly significant social and economic burdens [19]. According to the International Diabetes Federation (IDF), DM affects 415 million people worldwide, with a prevalence of 8.8%, and these values are expected to rise still further to 642 million by the year 2040, with a prevalence of 10.4% [20]. DPN is one of the most frequent complications of DM and usually characterized by gradually increases in pain severity, impairments in tactile and proprioceptive sensation, vibration sense, and improper postural control [21]. DPN is commonly associated with high rates of mortality and morbidity [22]. Acupuncture has been widely used in clinical practice for the treatment of DPN in China. However, so far there has been no appropriately designed randomized controlled trial to provide clear evidence about the effectiveness of acupuncture treatment for DPN at home and abroad.

In this study, the inclusion criterion of age, from 18 to 75 years, was chosen to cover age range as wide as possible. We cooperated with the endocrinology department of Long-Hua Hospital affiliated to Shanghai University of Traditional Chinese Medicine to ensure the required number of subjects recruited. During the study period, patients will receive routine health care as provided to all other patients with DPN. Usually, we encourage them not to change their medications, but adjusting medications will be permitted if necessary. We believe this strategy can reflect real-world practice and satisfy ethical obligations better.

A standardized treatment protocol will be utilized to assure reproducibility of the study. In this trial, the treatment protocol was based on traditional acupuncture theory, previous studies [15], and the consensus of endocrinologists and acupuncturists from Long-Hua Hospital affiliated to Shanghai University of Traditional Chinese Medicine. The amount of acupuncture is intensive, which is similar to clinical practice in China. Needles will be stimulated manually for at least 10 s at each acupoint and retained in place for 20 min. There will be 2 treatment sessions per week within the course of 12-week treatment, giving a total of 24 sessions.

A suitable control group is critical for a well-designed clinical trial. On the basis of literature review, using a blunt-tipped needle that does not penetrate the patient’s skin is the most commonly used approach for administering sham treatments among acupuncture trials [16, 17]. Patients who have received acupuncture treatment in the last 3 months and can distinguish SA from MA will be excluded. The same control group design, no skin penetration at acupoints, was adopted and succeeded in masking patients with DPN [7, 14, 15, 18]. Furthermore, all patients will be asked to guess which treatment they have received to test patient-blinding effects at week 12.

The change of nerve conduction velocity is chosen as the primary outcome because it is the highest sensitive and objective method to detect neuropathy. Multiple systematic reviews [11] recommended nerve conduction velocity as a main outcome, and it had been widely used as an outcome measure in DPN studies [23]. At the same time, assessment of the severity of DPN mainly depends on patient-reported outcomes. The MNSI is the most DPN-specific patient-reported measure. In this trial, we use the DSQL to evaluate quality of life in patients with DPN before and after acupuncture treatment. The DSQL captures the impact of detailed aspects of modern diabetes management (e.g., carbohydrate counting and flexible insulin dose adjustment) that is extensively used in evaluating quality of life in DM. The DSQL offers a valuable tool for assessing the impact of treatment approaches on QoL in adults with DM [20].

The limitation of our trial is acupuncturists are not blinded for the nature of intervention. We hope results of this trial will provide more reliable evidence and clarify the value of acupuncture as a treatment for DPN.

To summarize, this trial meets the methodological demand of adequate randomization and allocation concealment, blinding of patients, outcome assessors, and statisticians. Findings of this study will provide high-quality evidences for evaluating the efficacy and safety of acupuncture treatment for DPN.

## Trial status

This trial is currently recruiting patients. This is version 2.0 of the protocol, dated June 6, 2016. Recruitment began on 10 October 2016 and the anticipated end date is 31 December 2021.

## Data Availability

All de-identified data collected during the trial will be available for anyone who wishes to access 6 months after publication in accordance with FAIR principles.

## Abbreviations

ADA: The American Diabetes Association
AEs: Adverse events
BMI: Body mass index
BP: Blood pressure
CRF: Case report form
DM: Diabetes mellitus
DPN: Diabetic peripheral neuropathy
DSMB: Data and Safety Monitoring Board
DSQL: Diabetes Specific Quality of Life scale
FPG: Fasting plasma glucose
HbAlc: Glycated hemoglobin
2hPG: 2-h postprandial blood glucose
IDF: International Diabetes Federation
ITT: Intent-to-treat
MA: Manual acupuncture
MNAP: Motor nerve action potential amplitude
MNCV: Motor nerve conduction velocity
MNLP: Motor nerve action potential latent period
MNSI: Michigan Neuropathy Screening Instrument
PN: Peripheral neuropathy
QoL: Quality of life
SA: Sham acupuncture
SNAP: Sensory nerve action potential amplitude
SNCV: Sensory nerve conduction velocity
SNLP: Sensory nerve action potential latent period
